### 2.7. Outcomes

#### 2.7.1. Primary outcomes.

ADAS-Cog^[22]^ evaluates cognitive function: including memory, ability to use, orientation, language expression ability, attention, reasoning ability and other items, and the higher the score, the more severe the neurological impairment.

#### 2.7.2. Secondary outcomes.

Mini-mental state examination^[26]^ evaluates mental status, including five items: orientation; memory; attention and calculation, memory; and language ability.Activities of daily living^[22]^ assesses patients’ living ability: including 6 aspects related to physical self-care and 8 aspects related to the ability to use tools.Neuropsychiatric inventory questionnaire^[27]^ evaluates common mental and behavioral symptoms of dementia: including 12 items such as delusions, hallucinations, agitation, and unpleasant mood.Serum superoxide dismutase and homocysteine levels: Fasting venous blood was collected from the two groups in the morning before and after treatment. Serum superoxide dismutase levels were measured by enzyme-linked immunosorbent assay, and homocysteine levels were measured by circulating enzymatic method.

Two research assistants will collect data based on the above outcome measures at baseline, 12 weeks after treatment, and at the end of treatment. All patients will be followed for 24 weeks and efficacy evaluations will be completed in the clinic at Weeks 12 and 24 of follow-up.

### 2.8. Safety evaluation

Patients will be asked to report any abnormal reactions that occur during the study to the investigator. The details of all adverse events will be recorded in the CRF, including the occurrence time, the degree and duration, suspected cause, effective measures, and results. Blood routine, urine routine, and liver and kidney function were measured at baseline and at the end of treatment. Safety measures were assessed in all patients at the end of the study to assess the safety of the study protocol.

### 2.9. Data management and quality control

Any amendment or change to the protocol will be re-approved through the official procedure of our hospital ethics committee. An independent clinical research associate will periodically review the progress of the study. Trained study personnel will collect study data and record it on the CRF. To ensure the reliability of the data, personal information about potential and registered participants will be collected, shared, and kept in an independent repository to protect confidentiality before, during, and after the trial. Access to the database will be restricted to study personnel on this study team. Participants’ information will not be made publicly available and shared without written permission from participants.

### 2.10. Statistical analysis

The study results will be independently analyzed by Full Analysis Set and Per-Protocol Set, and the safety evaluation will be based on Safety Set. Statistical evaluation of Full Analysis Set will follow intent-to-treat. Missing values will be measured using the last observation carried forward method. Data from this study will be statistically analyzed using SPSS 21.0 software (IBM Company, New York, NY). Count and grade data were expressed as percentage (%), the measurement data of *χ*^2^ test or non-parametric test were expressed as mean ± standard deviation (*x* ± S) or interquartile range M (P25, P75), normal distribution was analyzed by *t* test, skewed distribution was analyzed by non-parametric test, and One-way analysis of variance multiple comparisons were used between multi-point repeated data groups, and differences were considered statistically significant when *P < *.05.

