## 1. Introduction

Alzheimer disease (AD) is a common cause of dementia, and the main clinical manifestations are aphasia, agnosia, and gradual loss of independent living ability.^[1]^ With the acceleration of the aging process of the population, the incidence rate of AD continues to rise. And the mortality rates of major diseases such as AIDS, stroke, and heart disease in the elderly in the United States have decreased over the past 15 years, with only AD increasing by 71%.^[2]^ The onset of the disease is insidious and progressively aggravated, generally with obvious symptoms after 2 to 3 years of onset, gradual memory, cognitive dysfunction, and behavioral abnormalities, and death due to complications such as pulmonary and urinary tract infections and pressure sores 10 to 20 years after onset.^[3]^ The pathogenesis of this disease is complex, and there is no effective drug that can reverse the disease process.^[4]^ It is important to take timely and effective therapeutic drugs and measures to delay the development of the disease.

Although researchers have made great efforts for the study of AD, there is no specific therapeutic drug at present. Cholinesterase inhibitors and memantine are drugs approved by the Food and Drug Administration and European Agency for the Evaluation of Medical Products for the treatment of AD, and although they can improve cognitive function and delay the disease in patients,^[5]^ they are not effective alone and have adverse effects on long-term use.^[6]^

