## 2. Materials and Methods

### 2.1. Study design

This is a prospective, randomized, single-blind, sham acupuncture controlled trial to study the clinical efficacy of acupuncture combined with Western medicine in the treatment of mild to moderate AD. Participants will be randomly divided into treatment and control groups. The treatment group will receive oral donepezil hydrochloride combined with acupuncture treatment, and the control group will receive oral donepezil hydrochloride combined with sham acupuncture treatment. After 24 weeks of continuous treatment, the participants will be followed up for 24 weeks. Flow diagram is shown in Figure 1, and study schedule is shown in Table 1. This experiment will follow the standard for reporting intervention in acupuncture controlled trials^[16]^ and the standard for reporting comprehensive trials.^[17]^

**Table 1 T1:** Study schedule.

Project	Stage				
	Screening period	Treatment period		Follow-up	
	Baseline	12-wk	24-wk	12-wk	24-wk
Record fill	√				
Fulfill inclusion criteria and exclusion criteria	√				
Sign informed consent	√				
Random allocation	√				
Treatment	√	√	√		
Effectiveness observation					
ADAS-Cog	√	√	√	√	√
MMSE	√	√	√	√	√
ADL	√	√	√	√	√
NPI	√	√	√	√	√
SOD and Hcy	√	√	√	√	√
Safety evaluation					
Blood test and urinalysis	√		√		√
Liver and kidney function	√		√		√
Record of adverse event		√	√	√	√

ADAS-Cog = Alzheimer disease assessment scale-cognitive subscale, ADL = activities of daily living, Hcy = homocysteine, MMSE = mini-mental state examination, NPI = neuropsychiatric inventory questionnaire, SOD = serum superoxide dismutase.

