#### 2.3.4. Standard for failing off and suspension.

The patient withdrew from the study for any reason.The principal investigator considered that the subject was not suitable for continuing the study.The subjects had poor compliance and changed the drug or added unspecified therapeutic drugs by themselves, which had an impact on the study results.Serious safety events occurred during the study and were assessed to be inappropriate for continuing the study.The patient was accidentally included after misdiagnosis or did not meet the inclusion and exclusion standard.

For all dropouts and patients who discontinue the trial, we will complete the last data test as far as possible. The dropout reasons and handling methods for all dropouts will be recorded on the case report form (CRF).

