### 2.4. Sample size

The sample size calculation in this study was based on the improvement of the score of the AD assessment scale-cognitive subscale (ADAS-Cog)^[22]^ after the end of treatment (the difference of the mean standard deviation of the ADAS-Cog score before and after treatment), referring to the results of the pretest, 6.65 ± 3.23 in the treatment group and 4.51 ± 2.11 in the control group, using the difference test, setting *α* = 0.05, *β* = 0.10. PASS15.0 (NCSS Company, Kaysville, UT) software calculated that 36 patients were needed in each group. The estimated withdrawal rate was 10%, and the total sample size required was 80 patients, 40 patients in each group.

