### 2.6. Intervention measures

Based on the recommendations of the EFNS guidelines for the diagnosis and management of Alzheimer disease,^[23]^ patients in two groups will receive oral donepezil hydrochloride 5 mg at bedtime (Weicai Pharmaceutical Co., Ltd., Shanghai, China, GYZZ H20050978, 5 mg/tablet) once a day for 24 weeks.

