#### 2.6.1. Acupuncture treatment.

This study will follow the international acupuncture clinical trial standard STRICTA to ensure the quality control of acupuncture treatment.^[24]^ Acupuncture points include: Baihui (GV20), Sishencong (EX-HN1), Dazhui (DU14), Shenmen (HT7), Shenshu (BL23), and Taixi (KI3).

To ensure the implementation of blinding, patients in both groups will wear eye masks during acupuncture, take the supine position, and the acupoints will be disinfected using 75% alcohol. An acupuncturist with a TCM license and at least 3 years of clinical experience will complete acupuncture treatment using a disposable stainless steel acupuncture needle (0.25 mm × 40 mm; Suzhou Hualun Medical Appliance Co., Ltd, Suzhou, China). The treatment group required acupuncture “Needling Sensation” (Deqi), and 0.5 cm non-acupoint needle insertion in the control group at a depth of 1 to 2 nn without requiring “Needling Sensation” (Deqi).^[25]^ Every other day for 30 minutes for 24 weeks.

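### Last observation carried forward is not limited to the treatment phase, so a patient lost after Week 24 enters the off-treatment follow-up comparisons with an on-treatment score

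*Protocol article*

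**What the plan says.** All of the following is in the protocol article.

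- **Missing data (section 2.10).** "Missing values will be measured using the last observation carried forward method". No visit, phase or outcome is named, and no other method is given. The Full Analysis Set follows intention to treat; a Per-Protocol Set is analysed as well but is not defined.
- **Treatment length.** Donepezil is given "once a day for 24 weeks" (section 2.6). The needling schedule is "Every other day for 30 minutes for 24 weeks" (section 2.6.1). Table 1 marks no treatment in the follow-up columns.
- **Follow-up.** "After 24 weeks of continuous treatment, the participants will be followed up for 24 weeks" (section 2.1). Section 2.7.2 adds: "All patients will be followed for 24 weeks and efficacy evaluations will be completed in the clinic at Weeks 12 and 24 of follow-up". Counted from the start of treatment, these visits are Weeks 36 and 48. ADAS-Cog is measured at both (Table 1).
- **Dropouts (section 2.3.4).** For these patients, "we will complete the last data test as far as possible".
- **Disease course (section 1).** "The onset of the disease is insidious and progressively aggravated".
- **Purpose.** Section 3 says that earlier trials lacked effective long-term follow-up and that this trial lengthened it to see the long-term effect.

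**The concern.** The follow-up visits ask whether a benefit gained on treatment lasts once treatment stops. For a patient seen at Week 24 and not again, the stated rule puts the Week 24 score into Weeks 36 and 48. It answers the question by assumption: for that patient, nothing was lost in the 24 weeks after treatment. The article itself describes the disease as one that worsens over time.

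The long-term comparison is at stake, one of two advances that section 3 claims over earlier trials. If the advantage of acupuncture fades and loss is equal in the two arms, the rule overstates what remains. If loss is unequal, the result also depends on which arm lost more patients.

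The rule does not do this to every missing score. A patient seen at Week 36 but not at Week 48 carries an off-treatment score, and a patient lost before Week 24 carries an earlier one. Where the final test in section 2.3.4 is done, that score is carried.

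**Working it through.** **Inputs.** Section 2.4 gives pretest ADAS-Cog improvements at the end of treatment of 6.65 (SD 3.23) and 4.51 (SD 2.11), 36 patients per group for 90% power, 10% withdrawal and 40 per group recruited. Assumptions: all loss rates other than 10%, the split between arms and the course after Week 24. The article gives none of these.

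**The plan's own figure.** The difference is 6.65 − 4.51 = 2.14 and the average SD is √((3.23² + 2.11²)/2) = 2.73. At two-sided α = 0.05 and 90% power, the normal approximation gives 35 per group. The Welch t test has power 0.898 at 35 and 0.906 at 36, so 36 is right, and 36/0.9 = 40. The sample size reproduces and is not in question.

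**Bias formula.** Let m_T and m_C be the shares of each arm last seen at Week 24, and a_T and a_C the true mean improvements at Week 48. If loss is unrelated to the scores, carrying forward shifts the Week 48 difference by

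m_T(6.65 − a_T) − m_C(4.51 − a_C).

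With equal loss m and a share r of the difference truly retained (a_T − a_C = 2.14r), this becomes m(1 − r) × 2.14.

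**Equal loss.**

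| Share lost, m | Nothing retained (r = 0) | Half retained (r = 0.5) |
|---|---|---|
| 5% (assumed) | 0.11 | 0.05 |
| 10% (planned) | 0.21 | 0.11 |
| 20% (assumed) | 0.43 | 0.21 |
| 30% (assumed) | 0.64 | 0.32 |

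The 10% row needs every withdrawal to fall between Weeks 24 and 36, so it is an upper limit for the planned rate. Suppose half of the lost patients are last seen at Week 36, when the difference has fallen to 1.07, and nothing remains at Week 48. The bias is then (m/2)(2.14) + (m/2)(1.07) = 0.16, 0.32 and 0.48 at 10%, 20% and 30%.

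**Unequal loss (assumed), both arms back at baseline.**

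- 20% acupuncture, 10% control: 0.2 × 6.65 − 0.1 × 4.51 = +0.88.
- 10% acupuncture, 20% control: 0.1 × 6.65 − 0.2 × 4.51 = −0.24.

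**Rejection rate with no true Week 48 difference.** Simulation with 40 per arm, the pretest SDs at both visits, within-patient correlation 0.5 and a Welch t test at two-sided 5%. Each patient is lost independently with the stated probability.

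| Loss | Both arms at baseline or 2 points below it | Both arms at 4.51 (control keeps its gain) |
|---|---|---|
| 10% | about 5–6% | about 6% |
| 20% | about 7–8% | about 10% |
| 30% | about 9–12% | about 17% |

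With 20% lost on acupuncture, 10% on control and both arms at baseline, the rate is about 20%, nearly all in favour of acupuncture.

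**The case against.** The strongest reply is about weight. The only documented loss rate is 10%, and the bias there is at most 0.21 points against a planned difference of 2.14. That rate was set for the end-of-treatment comparison, and patients lost before Week 24 carry no Week 24 score. If 5% are lost afterwards, the bias is 0.11. Nothing in the article suggests unequal loss: patients are blinded, and both arms have the same drug and needling schedule. The follow-up comparisons have no stated power or hypothesis. All of this stands and keeps the point modest.

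The Per-Protocol Set might leave out withdrawn patients and so give a companion result that depends less on carried scores. Because the article does not define it, this is partial mitigation at best.

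It can also be said that limits on imputation belong in an analysis plan that is not shown. Such a plan could narrow the rule. But the article states a rule in general terms, so the fault is in what is stated, not in missing detail.

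Stronger readings are tempting, and the documents do not support them:

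- **That the main efficacy result is biased by this.** Carrying Week 24 scores into follow-up does not touch the Week 24 comparison, on which section 2.4 rests.
- **That the withdrawal criteria in section 2.3.4 imply heavy loss in follow-up.** Section 2.7.2 says that all patients are followed, so no loss beyond ordinary withdrawal can be inferred.
- **That patients are off all treatment after Week 24.** Only protocol treatment is known to end; the article is silent on donepezil taken outside the protocol.

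In the other direction, one might argue that the test turns conservative if both arms decline. In simulation, rates below 5% appear only when exactly equal numbers are lost in each arm in every trial, which random loss does not give.

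**Conclusion.** The point holds, at modest weight. As written, the rule fills missing follow-up scores of patients last seen at Week 24 with on-treatment values, and so presumes the persistence under study. With equal loss and a fading advantage, the bias favours acupuncture: at most 0.21 ADAS-Cog points at the planned 10%, with a rejection rate of about 5–6%. It becomes material only at higher or unequal loss, and those rates are assumptions.

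The sizes rest on the pretest means and SDs in section 2.4, on loss unrelated to the scores and on the assumed off-treatment courses. If the full difference persists and loss is equal, the bias is zero. The change should be made because the long-term result is a declared aim and the repair is cheap.

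**What to change.** In section 2.10, state that no score from Week 24 or earlier is carried into the follow-up visits at Weeks 36 and 48. Analyse those visits with a mixed model for repeated measures on all observed ADAS-Cog scores, with terms for baseline score, arm, visit and arm by visit. Take the arm contrast at Week 48 as the estimate of persistence. A sensitivity analysis that imputes missing acupuncture-arm follow-up scores from the control-arm course would probe the model's main assumption, but it is optional.

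The cost is an amended paragraph, the ethics re-approval that section 2.9 requires and a little more analysis work. No visits or patients are added. The model assumes data missing at random. Its follow-up intervals would be up to about 1/√0.9 = 1.05 times as wide as with complete data at 10% loss, and up to 1.12 or 1.20 times at 20% or 30%.

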### 2.5. Randomization and blinding

Patients meeting the inclusion and exclusion standard will be randomized in a 1:1 ratio by a central web-based randomization tool to either the treatment group (acupuncture combined with oral donepezil hydrochloride) or the control group (sham acupuncture combined with oral donepezil hydrochloride). Random sequences were generated by an independent statistician using SAS 9.3 software (SAS Institute, Cary, NC). Research assistants entered patient information on a tablet computer and were assigned a random number to complete the random assignment based on the random number. Limited by the way of acupuncture, acupuncture operators were aware of the grouping results, and patients, other investigators, and data statisticians were not aware of the grouping results.

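### The distribution of the outcome data chooses between a t test and an unnamed rank test, and no listed analysis adjusts for baseline, so the primary ADAS-Cog effect measure is not fixed and precision is lost

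*Protocol article*

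**What the plan says.** Section 2.10 states three methods for continuous data:

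- "normal distribution was analyzed by *t* test"
- "skewed distribution was analyzed by non-parametric test"
- "One-way analysis of variance multiple comparisons were used between multi-point repeated data groups"

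It gives no rule for judging normality, does not name the non-parametric test, lists no baseline covariate, and does not say which method carries the primary ADAS-Cog comparison.

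Section 2.4 says: "The sample size calculation in this study was based on the improvement of the score of the AD assessment scale-cognitive subscale". It explains this in brackets as "the difference of the mean standard deviation of the ADAS-Cog score before and after treatment". The planning values are 6.65 ± 3.23 and 4.51 ± 2.11, giving 36 per arm and 80 patients in total after 10% withdrawal. Table 1 and section 2.7.2 show that ADAS-Cog is measured at baseline, twice during treatment and twice in follow-up.

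**The concern.** A t test and a rank test answer different questions. The trial is planned on a difference in means, and a rank test gives no estimate to set against 2.14 points. If the shape of the observed data decides which test is run, the primary effect measure is known only after the data are in. The one-way ANOVA clause adds a third candidate, because ADAS-Cog is itself measured at several time points.

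Every patient also has a baseline ADAS-Cog score, which should predict the later score. None of the three methods uses it as a covariate. Nor does section 2.10 say whether the t or rank test is applied to the change, as in section 2.4, or to the final score. Power can differ greatly between the two.

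**Working it through.** **Inputs from section 2.4.** Mean changes 6.65 and 4.51; SDs 3.23 and 2.11; α = 0.05; β = 0.10; 36 per arm; 10% withdrawal.

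**Assumed, not in the article.** The correlation ρ between baseline and end-of-treatment ADAS-Cog, taken as 0.5 to 0.9, with equal SDs at the two visits.

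**1. The plan's own figure.** Difference = 6.65 − 4.51 = 2.14. Common SD = √[(3.23² + 2.11²)/2] = 2.728. A two-sided noncentral-t calculation needs 36 per arm, with power 90.7% (90.6% with the Welch form). 36/0.9 = 40 per arm, 80 in total. The sample size reproduces and is not at fault.

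**2. Baseline adjustment.** With SD σ at each visit, the error variance per patient is:

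- change score: 2σ²(1 − ρ)
- final score: σ²
- ANCOVA: σ²(1 − ρ²)

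ANCOVA relative to change is therefore (1 + ρ)/2, a reduction of (1 − ρ)/2. The change SD of 2.728 implies σ = 2.728/√[2(1 − ρ)]. Power for 2.14 points at 36 per arm, two-sided 5%:

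| Assumed ρ | ANCOVA SD = 2.728√[(1 + ρ)/2] | Variance cut against change | Power, change t test | Power, ANCOVA | Implied σ | Power, final-score t test |
|---|---|---|---|---|---|---|
| 0.5 | 2.36 | 25% | 90.7% | 96.6% | 2.73 | 91% |
| 0.7 | 2.52 | 15% | 90.7% | 94.5% | 3.52 | 72% |
| 0.8 | 2.59 | 10% | 90.7% | 93.3% | 4.31 | 55% |
| 0.9 | 2.66 | 5% | 90.7% | 92.0% | 6.10 | 31% |

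**3. The two-step rule.** The article defines neither the normality check nor the rank test, so the simulation assumed Shapiro-Wilk at 0.05 in each arm, then a t test or Mann-Whitney, with 36 per arm and 20,000 runs per scenario. Means are equal in every row, and the skewed data are gamma with shape 4.

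| Data | Sent to rank test | Type I error, two-step rule | Type I error, t test alone |
|---|---|---|---|
| Normal, equal SDs | 10% | 5.1% | 5.0% |
| Normal, SDs 3.23 and 2.11 | 10% | 5.2% | 5.0% |
| Skewed, equal SDs | 78% | 5.3% | 5.0% |
| Skewed, SDs 3.23 and 2.11 | 77% | 7.8% | 5.3% |

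The excess in the last row arises because the rank test does not test equality of means. With normal data at the planned difference and SDs, the two-step rule has 90.6% power against 90.8% for the t test, so little power is lost there.

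**The case against.** The strongest case on the other side is that this is a matter of efficiency. A t test on change is a legitimate analysis and already meets the 90% target. The rule is stated in advance, and section 2.5 keeps the statisticians unaware of allocation, which limits any steering towards a preferred result. The choice of covariates is often left to an analysis plan, which is not shown here. Much of this stands, and it keeps the point moderate. It does not remove it: the article itself states the data-dependent choice, and blinding the statistician does not fix the effect measure.

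Three stronger readings are tempting and are not supported.

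- **That the trial disregards baseline.** Section 2.4 powers on the before-to-after change, and a test on change uses the baseline score, though less efficiently than ANCOVA. What can be said is that no stated method adjusts for it.
- **That chance baseline imbalance could distort the result by a large part of the planned effect.** At ρ = 0.8 the standard error of the baseline difference between arms of 40 is 4.31 × √(2/40) = 0.96 points. Only (1 − ρ) of an imbalance carries into a change comparison: 0.2 × 0.96 = 0.19 points, 9% of 2.14. The unadjusted standard error already allows for it. Nor does the description of randomisation ("will be randomized in a 1:1 ratio by a central web-based randomization tool") show that stratification is absent, since a condensed article may omit it.
- **That the two-step rule generally inflates false positives.** It did so in one of the four scenarios, where skew and unequal SDs coincide.

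It is also an inference that the t or rank test is the primary comparison, because the ANOVA clause could be read as covering ADAS-Cog. That strengthens the point that the primary analysis is not fixed.

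**Conclusion.** The point holds with moderate weight. As written, section 2.10 does not fix whether the primary ADAS-Cog result will be a mean difference or a rank comparison, and it uses the baseline score less efficiently than it could. The unfixed effect measure follows from the text alone and needs no assumption.

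The sizes do rest on assumptions. The rise in power of 1.3 to 5.9 percentage points over a change-score t test depends on ρ from 0.9 down to 0.5 and on equal SDs at both visits. The larger exposure, power as low as 31%, arises only if the test is run on the final score and ρ is high; the article leaves that open but does not say it will happen. The type I error of about 8% depends on the assumed skew together with the planned SDs, and on the assumed form of the normality check.

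**What to change.** State in section 2.10 that the primary analysis is an ANCOVA of ADAS-Cog at the end of treatment (Week 24 of the treatment period), or of its change from baseline, with arm and baseline ADAS-Cog as terms. The Week 24 contrast of a repeated-measures model with baseline as covariate would serve equally well. Report the adjusted mean difference with its 95% confidence interval. Because the planned SDs differ (3.23 and 2.11), heteroscedasticity-robust standard errors are preferable.

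Remove the normality-based choice of test for continuous outcomes. Keep a named rank test or a bootstrap interval as a sensitivity analysis only. Treat the continuous secondary outcomes in the same way, each with its own baseline.

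The cost is a change of wording and one model term (one degree of freedom). No new data, visits or patients are needed, and the planned 80 can stand. The change should be made before outcome data are examined by arm.

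### One-way ANOVA is named for the repeated visits although each patient gives five correlated scores; it is the wrong method for the longitudinal comparisons, though a valid t test of Week 24 change remains available

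*Protocol article*

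**What the plan says.** Section 2.10 of the protocol article gives two rules for continuous outcomes. The general rule is that "normal distribution was analyzed by *t* test, skewed distribution was analyzed by non-parametric test". For data collected at several times, it says that "One-way analysis of variance multiple comparisons were used between multi-point repeated data groups". No repeated-measures ANOVA, mixed model or other method with a patient-level term is named.

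The visits are set out in section 2.7.2: data are collected "at baseline, 12 weeks after treatment, and at the end of treatment", and then "efficacy evaluations will be completed in the clinic at Weeks 12 and 24 of follow-up". Table 1 agrees. ADAS-Cog, MMSE, ADL, NPI and the two serum markers are each measured at all five times.

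Section 2.4 bases the sample size on the difference in "ADAS-Cog score before and after treatment", taking "6.65 ± 3.23 in the treatment group and 4.51 ± 2.11 in the control group". Section 2.7.1 makes ADAS-Cog the primary outcome. Section 2.10 also fills missing values by carrying the last observation forward.

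**The concern.** One-way ANOVA has a single factor and assumes independent observations. Five scores from one patient are not independent. With no patient term, the method cannot separate variation between patients from variation within them. With no arm-by-visit term, it cannot test jointly whether the arms diverge over time.

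The Discussion says that follow-up was lengthened to observe long-term effects, so the comparisons over time carry part of the trial's purpose. An analyst who follows the sentence literally would get wrong standard errors for contrasts that pool visits or compare them. ADAS-Cog is itself measured repeatedly, so the sentence could be read as covering the primary outcome, and nothing in section 2.10 assigns that outcome to the t test instead.

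This is a method stated wrongly, not a detail left to a later document. An analysis plan would have to contradict the sentence to repair it.

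**Working it through.** **1. The plan's own figure.** Inputs from section 2.4: difference 6.65 − 4.51 = 2.14; SDs 3.23 and 2.11; α = 0.05; power 0.90. The root-mean-square SD is √((3.23² + 2.11²)/2) = √7.4425 = 2.73. For a two-sided two-sample comparison, the normal approximation gives 35 per arm. The exact t calculation gives 89.9% power at 35 and 90.7% at 36, so 36 is reproduced. Then 36/0.9 = 40 per arm, 80 in total. This calculation compares change scores between two arms and does not involve the ANOVA sentence.

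**2. Assumption.** The article gives no within-patient correlation. I take the same rho between every pair of visits and show 0.3 to 0.9.

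**3. Four post-baseline visits pooled, arm as the factor.** The variance of the arm mean is understated by the design effect DE = 1 + (4 − 1)·rho. The true type I error is 2·(1 − Φ(1.96/√DE)). The simulation is under the null, with 36 per arm and 10,000 runs.

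| rho | DE | Type I error, formula | Type I error, simulation |
|---|---|---|---|
| 0.3 | 1.9 | 0.155 | 0.147 |
| 0.5 | 2.5 | 0.215 | 0.217 |
| 0.7 | 3.1 | 0.266 | 0.271 |
| 0.8 | 3.4 | 0.288 | 0.295 |
| 0.9 | 3.7 | 0.308 | 0.305 |

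For change scores, two changes from the same baseline have covariance σ²(1 − rho) and variance 2σ²(1 − rho). They therefore correlate 0.5 whatever rho is. DE = 1 + 3 × 0.5 = 2.5 and the type I error is 0.215. Simulation with 40 per arm gave 0.20 to 0.22.

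**4. Visit as the factor within an arm.** One-way ANOVA uses variance 2σ²/n for the difference between two visit means. The true variance is 2σ²(1 − rho)/n. The standard error used is therefore 1/√(1 − rho) times the true one.

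| rho | SE used / true SE | Null rejection rate of the visit F test (nominal 0.05) |
|---|---|---|
| 0.3 | 1.20 | 0.010 |
| 0.5 | 1.41 | 0.001 |
| 0.7 | 1.83 | <0.001 |
| 0.8 | 2.24 | <0.001 |
| 0.9 | 3.16 | <0.001 |

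A test that almost never rejects under the null also misses real change.

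**5. Ten arm-by-visit cells as one factor.** The overall test rejects at 0.033 to 0.061 under the null for rho 0.3 to 0.9. Between-arm contrasts at one visit stay near 0.05. Between-visit contrasts have the fault in step 4.

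**6. One visit at a time.** With two arms this is the t test. The simulated null rejection rate is 0.049 to 0.052 for rho 0.3 to 0.9, so it is valid.

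**7. Methods that respect the patient as the unit.** An arm comparison of patient means, and a repeated-measures F test for visit, both reject at 0.046 to 0.051 under the null over the same range of rho.

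**The case against.** The strongest reply is that the main comparison is already sound. Section 2.4 sizes the trial on a two-arm difference in change, and section 2.10 names a t test for normally distributed data. A t test of Week 24 change needs no independence across visits. That stands. A reader might infer that every P value in the trial is invalid, or that no valid between-arm test exists at Week 24 or at the end of follow-up. The documents do not support this, because a t test of change at either time is valid. What is missing is a valid joint analysis over visits, and a statement of which method governs the primary outcome.

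A second reply is that nothing in section 2.10 says visits are pooled. That also stands. Of the four layouts examined, only pooling by arm inflates false positives substantially, so the 16–31% holds only under that reading.

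A third is that the sentence may mean a separate ANOVA at each visit, or may be loose wording for repeated-measures ANOVA. With two arms, the first is just the t test already named and leaves the multiple comparisons without an object. The second concedes that the wording needs correcting.

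A reader might also infer that the planned power is lost because raw scores would be compared visit by visit. The article does not say that raw scores will be used, and section 2.4 defines the quantity as change. Any such loss would come from using raw scores rather than change and would be the same for a t test. With equal SDs at both visits, it would not arise at rho of 0.5 or below.

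**Conclusion.** The concern holds for the longitudinal comparisons. Section 2.10 names a method that ignores the five correlated scores per patient and has no arm-by-visit term. The error can go either way. With post-baseline visits pooled by arm, type I error is about 16–31% (about 21–22% on change scores) against 5%. With visits treated as independent groups, standard errors for within-patient change are 1.2 to 3.2 times too wide. These ranges rest on an assumed rho of 0.3 to 0.9, equal between all visits.

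The Week 24 t test of ADAS-Cog change is not harmed, and the sample size stands. The sentence should be corrected before analysis; the design does not need to change.

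**What to change.** Delete the one-way ANOVA sentence from section 2.10. State that the primary comparison is the difference between arms in ADAS-Cog change from baseline to Week 24 of treatment.

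Analyse the repeated visits with a model that has a patient-level covariance and an arm-by-visit term. One suitable choice is a mixed model for repeated measures with arm, visit, arm-by-visit, baseline score and baseline-by-visit, reporting the between-arm contrast at each visit. Other models with these two features would also cure the fault.

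Fit the model to observed data. Section 2.10 currently carries the last observation forward, and a mixed model given those values would treat copied scores as real measurements. The missing-data sentence must therefore be changed for this analysis as well.

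The cost is analysis wording and syntax. No patients, visits or data are added.
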